## Abstract

**Introduction:**

Lower limb revascularization with inguinal incisions is a common vascular surgical procedure. Due to risk of injury to lymphatic vessels and a diverse bacterial flora in the groin, surgical site infections (SSI) represent a common and sometimes life-threatening complication. While transverse incisions in endovascular aneurysm repair has a low SSI rate, vertical incisions in thrombendarterectomy (TEA) has a higher risk and bypass the highest risk. This randomized controlled trial (RCT) will investigate the protective role of negative pressure wound therapy (NPWT) on closed inguinal incisions in elective vascular surgery undergoing TEA and bypass procedures, respectively, to prevent SSI.

**Methods:**

This RCT registered at ClinicalTrials.gov (Identifier: NCT01913132) compares the effects of a NPWT dressing (PICO™, Smith & Nephew, UK) to standard wound dressing on postoperative SSI. The multi-center study includes two distinct vascular procedures with different SSI risk profiles: TEA and lower limb bypass. Three hundred and fifty-eight groin incisions are anticipated to be included in the TEA group and 133 inguinal incisions in the bypass group. Bilateral inguinal incisions will be randomized to NPWT in one groin and control dressing in the contralateral groin, and this dependency was accounted for in sample size calculation and will be addressed in data analysis.

**Discussion:**

This RCT attempts to evaluate the potential benefit of NPWT on closed inguinal incisions after two distinct vascular procedures at high risk of SSI. Outcome of this trial could have implications on postoperative wound care in both vascular and non-vascular surgical patients.

## Introduction

1

Lower limb revascularization relies on access to the common femoral artery. The inguinal region contains, however, a high concentration of virulent bacteria [1] due to its close proximity to the perianal region and open lower limb revascularization is associated with increased risk of surgical site infections (SSI). Meticulous surgical technique during open vascular surgery is necessary to minimize the risk of postoperative lymphatic wound complications [2]. Both patient- and procedure-related factors contributes to the risk for surgical site infections (SSI) [3]. It appears that extension of incisions are associated with increased risk of SSI during open vascular procedure [4]. Prospective series on open lower limb revascularization is not seldom associated with SSI rates of more than 20% [5]. Apart from being common, consequences may be devastating as severe deep SSI may lead to severe bleeding complications and/or limb loss and/or death.

Negative pressure wound therapy (NPWT) on closed, clean incisions, has emerged as a prophylactic option to reduce the risk of SSI in high-risk incisions [[6], [7], [8]]. A recent meta-analysis on randomized control trials (RCT) compared NPWT to standard dressing for closed groin incisions after vascular surgery and found a reduced SSI rate. This meta-analysis relied on the use of Prevena™ NPWT system. No RCT has been published using the alternative PICO™ device on vascular surgical incisions. In contrast to Prevena™, PICO™ is a canisterless, disposable NPWT system, where the dressing pad works mainly by evaporation of fluid [9]. NPWT decreases hematoma and seroma formation mainly by enhancing the endogenous draining capacity of the lymphatic system [10]. NPWT induces less biomechanical stress around skin and subcutaneous suture lines [11], which probably facilitate tissue apposition creating a better microbial barrier and decrease scar formation. There appear to be little perfusion changes around the wound edges measured by laser Doppler velocimetry before and after application of PICO™ on incisional wounds [12].

Patients undergoing inguinal vascular surgical incisions have very different SSI rate due to indication of surgery and procedure. While patients undergoing elective endovascular aneurysm repair (EVAR) have a low inguinal SSI rate of a few percent, those undergoing elective open lower limb revascularization have SSI rates around 30% [13]. Based on these different SSI rates, two sample size calculations were conducted and two separate RCTs launched [14]. However, patients undergoing elective open lower limb revascularization is very heterogenous in terms of SSI risk. Those undergoing lower limb bypass surgery has double as high SSI risk as the group undergoing local thrombendarerectomy (TEA) [15]. Therefore, a study protocol for a multi-centre RCT on incisional NPWT compared to standard dressing in two subgroups, local TEA group and bypass group, was found warranted.

## Materials and methods

2

*Overall design:* Multi center randomized controlled clinical trial.

### Study objectives

2.1

The study was initiated to determine whether a prophylactic negative pressure wound therapy pad (PICO™) applied after vascular surgical procedures with inguinal incisions could reduce the surgical site infection rate as well as the frequency of other wound complications such, seroma/lymphocele, hematoma and wound dehiscence when compared to the standard wound dressing.

### Endpoints

2.2

The primary endpoint is the SSI rate and secondary endpoints are the rate of seroma/lymphocele, hematoma and wound dehiscence within the first 90 days postoperatively.

### Setting

2.3

This study is a multi-centre study including vascular centers at Skåne University Hospital, Malmö, Örebro University Hospital, Jönköping county hospital and Blekinge county hospital Karlskrona. Dedicated research nurses at each centre will keep track on inclusion, monitoring and follow up of the patients.

### Eligibility criteria

2.4

All adult patients undergoing elective vascular procedures with incisions for arterial exposure at the lower limb are eligible to participate.

### Enrollment and randomization

2.5

Patients scheduled for lower limb revascularization are provided with written information prior to undergoing the admission procedure which takes place one to two weeks prior to scheduled surgery. During the admission process, the background and aim of the study are discussed with eligible patients, informed consent obtained and the randomization conducted by outpatient clinic nurses. In this study we apply simple randomization using an opaque randomization envelope containing equal numbers of “PICO” and “standard” notes. In bilateral groin incisions, the draw from the envelope dictates the wound dressing selection in the right inguinal incision and the contralateral incision is automatically assigned the alternate dressing. Randomization outcome and consent form are documented in the patient's records.

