A potential limitation of this study could be that the randomization takes place before the operation, not at its end. One might argue that this could create bias since the surgeon in charge, could be aware of the respective randomization outcome before conducting the operation and thereby subconsciously or consciously modify their behavior and surgical technique. Because of the large staff turn-over in the operation room, an intraoperative randomization would most likely have led to a very large number of patient dropouts due to insufficient sense of awareness for the study and the principal investigator felt that intraoperative computer-generated randomization not seems feasible. Use of randomization envelopes in the operation room was not felt as an option either due to issues of management of these envelopes and the large turnover of personnel at present times. When wound closure has been performed, the surgeon usually leaves the operation room and the scrub nurse finalizes the wound care including application of wound dressings. That is usually the time to take a look at the randomization results in the patient files, which should minimize bias due to behavior issues. At present time, four vascular centers will be enrolling patients into the study and these centers does not, for instance, have identical perioperative wound care. The type of standard wound dressing used in the control arm might differ. We will, however, document the type of wound dressing and perform sub analysis accordingly. Generalizability of the results will be better in a multi-centre trial including both university hospitals and county hospitals.

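### Allocation by drawing a note from an envelope at the admission visit follows no pre-assigned sequence, cannot be audited as described, and leaves balance within procedure and centre uncontrolled

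*Protocol article*

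**What the plan says.** Protocol article, section 2.5 (Enrollment and randomization):

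- Method: "we apply simple randomization using an opaque randomization envelope containing equal numbers of" PICO and standard notes.
- Who and when: "informed consent obtained and the randomization conducted by outpatient clinic nurses", during "the admission procedure which takes place one to two weeks prior to scheduled surgery".
- Bilateral cases: "the draw from the envelope dictates the wound dressing selection in the right inguinal incision", and the other groin receives the alternative dressing.
- Record: "Randomization outcome and consent form are documented in the patient's records".

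Section 5 (Discussion) names one limitation of the randomisation: it takes place before surgery, so the surgeon may know the result. It explains why allocation is not done in theatre: "intraoperative computer-generated randomization not seems feasible", and envelopes there are ruled out because of staff turnover. It also says that the four centres do not share identical perioperative wound care, and "The type of standard wound dressing used in the control arm might differ".

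TEA and bypass are sized separately in section 3.2, at 358 and 133 groin incisions. Section 3.1 gives their infection risks as 22.2% and 41.1%. The tests in section 4 (Fisher's exact, McNemar, combined p-value) do not include centre.

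**The concern.** The article positively describes a draw of notes from an envelope by staff at the visit where patients are enrolled. Opacity hides a note until it is drawn. It does not tie a given patient to a given note in advance. The patient's record shows the note that was accepted, not whether another was drawn first. A sequence fixed beforehand and held by someone else removes both possibilities; this draw does not.

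Concealment matters here because staff who know a patient's wound risk may have a view on which dressing that patient should get. If allocation can follow risk, the comparison is biased, and no later analysis reliably removes that.

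There are two lesser problems. The term *simple randomization* conflicts with a finite envelope of equal numbers unless notes go back in. And procedure and centre, which bear on infection risk, wound care and control dressing, play no stated part in the allocation.

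**Working it through.** **1. The plan's own sample sizes.**

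Inputs from section 3.2: 20% vs 8% (TEA) and 40% vs 15% (bypass), 5% level, 80% power, n1 = 284 and 112, n2 = 210 and 93, unilateral shares 0.95 and 0.90.

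- Exact two-sided Fisher power is 0.802 at 142 per arm and 0.808 at 56 per arm, so n1 reproduces.
- The normal-approximation McNemar formula gives 106.6 pairs (213 groins, against 210) and 47.8 pairs (95.6 groins, against 93), which is close.
- TEA: 0.95 × 284 + 0.05 × 210 = 280.3; 280/(1 − 0.139) = 325; 325 + 33 = 358.
- Bypass: 0.90 × 112 + 0.10 × 93 = 110.1; 110/(1 − 0.089) = 121; 121 + 12 = 133.

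None of this depends on how notes are drawn, so a better allocation method leaves both totals as they are.

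**2. What chance imbalance costs.**

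Under true simple randomisation the size of one arm is Binomial(N, 0.5).

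| Group | N (n1) | 95% range of one arm | Power at exact 1:1 | Power averaged over splits |
|---|---|---|---|---|
| TEA | 284 | 125–159 | 0.802 | 0.819 |
| Bypass | 112 | 46–66 | 0.808 | 0.827 |

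Power is not lost. The slight gain at uneven splits reflects the discreteness of the exact test.

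Within a centre the spread is wider in relative terms. In an assumed cell of 34 (about 133/4), one arm ranges from 11 to 23. In an assumed cell of 20, a split of 14:6 or worse has probability 2 × P(Bin(20, 0.5) ≤ 6) = 0.115.

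If centre infection rates had a standard deviation of 10 points (assumed), chance centre imbalance would move the bypass contrast with a standard deviation of about 2 × 0.10/√112 = 0.019. That is 1.9 points against a 25-point target. It is random variation, not bias.

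**3. Simple, or an equal-note pool?**

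If each note is returned, draws are independent and the term is right, but no note is used up that could later be reconciled with patients.

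If notes are kept out and someone keeps a tally, the expected number of correct best guesses over 2n notes (Blackwell–Hodges) is n + 2^(2n−1)/C(2n, n) − 1/2. The envelope size is not given, so a range is shown:

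- 10 notes: 5 + 512/252 − 0.5 = 6.53, or 65%.
- 20 notes: 62%.
- 100 notes: 56%.

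True simple randomisation gives 50%.

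**4. Illustration of steering (behaviour assumed; no true effect; TEA overall risk 20%).**

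Let a share s of patients have twice the risk of the rest. The usual risk is x = 0.20/(1 + s). If all of them end up on one dressing and the rest split evenly, that arm has risk x(1 + 3s)/(1 + s) and the other has x. The bias is 0.40 s/(1 + s)².

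- s = 0.05: 1.8 points.
- s = 0.10: 3.3 points. With 280 patients, (126 × 0.1818 + 28 × 0.3636)/154 = 21.5% vs 18.2%.
- s = 0.20: 5.6 points.
- s = 0.10, but only half of the high-risk patients who first drew the other dressing are redrawn (high-risk split 21:7): x × 168/147 − x × 140/133 = 1.6 points.

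The target difference is 12 points. Steering high-risk patients to PICO hides a benefit; steering them away creates a false one.

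**5. Do the stated reasons cover the method used?**

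The Discussion rejects computer allocation and envelopes for the operating room. Section 2.5 places allocation at the admission visit one to two weeks earlier, where theatre staff turnover plays no part.

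**The case against.** **The article is a condensed account.** It does not say how many notes there are, whether each centre holds its own envelope, how notes are stored or whether draws are logged. Section 2.3 has dedicated research nurses tracking inclusion, and the result is written into the record. All of this stands. It would be wrong to assert that there is one envelope for the whole trial or that no log exists, and one envelope per centre would in effect separate allocation by centre. What remains is the mechanism that the article does state: drawing from a pool of equal notes does not fit a numbered, pre-assigned sequence.

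**Unstratified randomisation is valid.** This also stands. A reader might infer that the procedure groups are unbalanced by design. The documents do not support that: allocation is 1:1 in expectation in each group, bilateral cases are balanced exactly within the patient, and power hardly moves. The plan also offers a sub-analysis by control dressing (section 5) and a sensitivity analysis for important baseline differences (section 4).

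**No tampering is shown, and the steering figures are invented behaviour.** Correct. A reader might take the 3.3 points as an estimate of bias in this trial. It is not: the share, the doubled risk and the complete steering are all assumed, and the direction is open. If staff preferred PICO for high-risk groins, the bias would run against PICO.

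**Predictability needs kept-out notes and a tally.** The article states neither, so that part is conditional.

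**Conclusion.** The point holds as a weakness of allocation concealment. The stated draw has no pre-assigned order and is made by clinic nurses at the enrolment visit, so a redraw or a non-entry after the note is seen could be neither prevented nor detected from what is described. The size of any resulting bias is unknown; the scenarios above run from 1.6 to 5.6 points in either direction under assumed behaviour.

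The randomisation label and the described envelope agree only if notes are returned, and the article should say which applies. Balance within procedure and centre is not controlled. That is a missed opportunity for prognostic balance in small centre cells, not a bias and not a loss of power.

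The conclusion rests on reading section 2.5 as it stands. Custody rules in a fuller protocol could reduce the risk but would not turn this draw into a concealed sequence. The change should be made, because selection bias cannot be repaired afterwards in the analysis.

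**What to change.** **Remaining patients** (the Discussion says that enrolment was not complete at publication):

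- Use a pre-generated permuted-block list with varying block sizes, stratified by planned procedure (TEA or bypass) and centre, held by someone independent of the enrolling nurses.
- Issue it at the admission visit, centrally or by sequentially numbered sealed opaque envelopes, and log the patient before the allocation is revealed.
- Keep the right-groin rule for bilateral cases.

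As a guide, blocks of 4 (assumed) in four centres would hold the arm difference per procedure to at most 4 × 2 = 8, leaving aside the few bilateral patients who use up list positions. Under simple randomisation the mean absolute difference is about √(2N/π): 13 for 284 TEA incisions and 8 for 112 bypass incisions.

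**Patients already randomised:** report the number of notes, whether they were returned, how many envelopes each centre had, and how draws were recorded.

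**Analysis:** keep the planned primary tests. Add a centre-adjusted sensitivity analysis within each procedure, and report results by allocation period.

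**Cost:** a protocol amendment, one list and a short added analysis, with the same staff and the same visit. The totals of 358 and 133 stay. The drawback is two allocation methods in one trial, which must be reported openly.

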### Ethical considerations

2.6

Informed consent was obtained from all patients. The study has been registered at ClinicalTrials.gov (Identifier: NCT01913132) and approved by the regional ethical review board (Dnr 2013/322), and supplementary ethical applications were approved for the inclusion of three additional vascular centers in Örebro, Jönköping and Karlskrona (Dnr 2016/886; Decision 20161028, Dnr 2018/309; Decision 20180419, and Dnr 2019/1387; Decision 20190227, respectively).

### The wound dressings

2.7

There is no difference between the surgical procedures and perioperative care between the treatment and control groups. At the end of the procedure, vertical incisions are closed according to surgeon's preference. Steri-Strips™ (3 M, St Paul, Minnesota) are often applied in case of intracutaneous sutures.

*PICO**™* is a negative pressure system employing −80 mmHg continuous suction generated through a canister-free portable pump. It is directly applied onto the closed incisions and, according to the manufacturer's recommendation, left in place for seven days, after which it stops working and can be removed by the patients themselves or nurses at the center's outpatient clinic. Each vascular centre will use their standard wound dressing, which consists of a sterile water-proof bandage with absorbent pad.

### Data collection and management

2.8

All data is collected using SPSS, version 25.0 (SPSS Inc., Chicago, Illinois, USA). The data stem from the patient's electronic records as well as content from conducted phone interviews after three months postoperatively. Visits at the outpatient clinic are scheduled in line with the clinic's and the Swedish vascular registry's guidelines at one and twelve months postoperatively.

#### Preoperative data

2.8.1

Data collected preoperatively are official Swedish identification number, age at operation, date of procedure, indication for procedure, gender, height (in cm), weight (in kg), body mass index (BMI, in kg/m2), ischemic heart disease (yes/no), atrial fibrillation (yes/no), arterial hypertension (yes/no), diabetes mellitus (yes/no), type of diabetes mellitus (regulated with diet only, oral anti-diabetic drugs, insulin-dependent), current smoker (yes/no), ex-smoker (yes/no), history of cerebrovascular insult (yes/no), previous inguinal surgery on the side where the groin incision is performed (yes/no), previous extracardiac vascular surgery (yes/no), critical ischemia (yes/no), Rutherford classification for severity of lower extremity arterial disease, foot wound (yes/no), anticoagulation with warfarin (yes/no), rivaroxaban (yes/no) or dabigatran (yes/no), American Society of Anesthesiologists (ASA) score, use of systemic corticosteroids (yes/no), use of acetylsalicyclic acid (yes/no), type of procedure, groin (right/left), randomization (PICO/standard dressing).

#### Perioperative data

2.8.2

Preoperative antibiotic treatment excluding antibiotic prophylaxis (yes/no), preoperative antibiotic prophylaxis received (yes/no), preoperative anemia (yes/no), preoperative blood glucose concentration (mmol/L), preoperative albumin concentration (g/L), preoperative estimated glomerular filtration rate (ml/min), form of anaesthesia (general/regional/local), groin incision performed (yes/no), bilateral incision (yes/no), vertical incision (yes/no), transverse incision (yes/no), use of wound products such as Floseal® (yes/no), Hemopatch® (yes/no), Tachosil® (yes/no) (all Baxter Healthcare Corporation, Deerfield, IL, USA), Collatamp® (EUSA Pharma, Oxford, UK) (yes/no), hybrid procedure (yes/no), synthetic graft used (yes/no), bovine pericardial patch used (yes/no), any patch used (yes/no), any foreign material applied in wound (yes/no), vein graft/patch (yes/no), arterial graft (yes/no), duration of procedure (min), bypass (yes/no), wound closure technique (resorbable intracutaneous/non-resorbable mattrace sutures/staples), wound dressing received (PICO™/standard) (Fig. 1), type of standard dressing (Vitri Pad/OPSITE Post-op Visible), postoperative antibiotic therapy (yes/no), number of transfused units of packed red blood cells, postoperative treatment at intensive care unit (yes/no), inpatient length of stay (days).

#### Follow-up data

2.8.3

Readmission within 30 days postoperatively (yes/no), surgical site infection (SSI) within 30 days (yes/no), wound culture obtained within first 3 months postoperatively (yes/no), reoperation 30 days (yes/no), sought medical attention because of groin problem within 90 days (yes/no), reoperation 90 days (yes/no), SSI 90 days (yes/no), reoperation 1 year (yes/no), SSI 1 year (yes/no), wound cultures within 1 year (yes/no), 1 year mortality (yes/no), mortality due to groin infection (yes/no), type of bacterial isolate, SSI severity grading according to Szilagyi classification [16], C-reactive protein concentration at infection diagnosis (mg/L), presenting symptoms, surgical revision (yes/no), negative pressure wound therapy after surgical revision (yes/no), sepsis (yes/no), bleeding (yes/no), wound dehiscence (yes/no), seroma (yes/no), hematoma (yes/no), lymphorrhea (yes/no), amputation within 1 year (yes/no). Adverse events of the NPWT dressing (yes/no) and type of adverse events.

The diagnosis SSI is made according to the 1999 diagnostic criteria defined by the Centers for Disease Control and Prevention, USA [17]. Wound outcome will be objectively evaluated with the validated ASEPSIS score [18]. The wound score is based upon the following criteria: Antibiotics (10 points), drainage of pus under local anaesthesia (5 points), debridement of wound (general anaesthesia) (10 points), serous discharge, erythema, purulent exudate, separation of deep tissue within the first week (5 points each), isolation of bacteria (10 points), stay as inpatient prolonged over 14 days (5 points). A total score ≥21 points is considered as infection, 11–20 points as disturbance of healing, 0–10 points as satisfactory healing. SSI along surgical incisions for exposure of arteries will be assessed. The data analysis and subsequent establishment of the diagnosis SSI or other wound complications is done under blinded conditions. The assessor at the outpatient clinic at one month and at one year does not know whether a particular groin incision was treated with NPWT or the standard wound dressing.

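### The only dressing adverse-event item is worded for the NPWT dressing, so reactions attributed to the dressing cannot be compared between arms

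*Protocol article*

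**What the plan says.** Section 2.8.3 (Follow-up data) lists the variables recorded after surgery. One concerns harms of the dressing itself: "Adverse events of the NPWT dressing (yes/no) and type of adverse events". The other items carry no restriction by arm, for example "wound dehiscence (yes/no), seroma (yes/no), hematoma (yes/no), lymphorrhea (yes/no" and "sought medical attention because of groin problem within 90 days (yes/no".

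The comparator is a real dressing and may differ between centres. Section 2.7 says: "Each vascular centre will use their standard wound dressing, which consists of a sterile water-proof bandage with absorbent pad". Section 2.8.2 (Perioperative data) records which product was used, "type of standard dressing (Vitri Pad/OPSITE Post-op Visible"), but lists no adverse-event item for it.

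Section 2.2 sets SSI as the primary endpoint and adds that "secondary endpoints are the rate of seroma/lymphocele, hematoma and wound dehiscence within the first 90 days postoperatively". Dressing reactions are not among the endpoints. In bilateral cases section 2.5 gives one groin the drawn dressing and "the contralateral incision is automatically assigned the alternate dressing", so these patients wear both dressings at the same time.

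**The concern.** A reaction under a dressing is informative about NPWT only against the background rate under the dressing it would replace. If reactions are asked about on the NPWT side alone, each one counts against NPWT, including those that the standard dressing would also have caused. The excess cannot be estimated, and no later analysis can recover data that were not collected.

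This matters because the Discussion looks ahead to effects on wound care in vascular patients and in other specialties. A decision to use NPWT preventively weighs fewer infections against any additional dressing harm, and for that harm the item as worded gives a one-arm count. It also gives up the within-patient comparison that bilateral cases could provide at almost no cost.

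**Working it through.** No arithmetic applies. The article states no rate, sample size or power for dressing adverse events, so there is no figure to reproduce. The check is to set the data-collection and endpoint sections side by side and ask what each arm can supply.

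1. **Dressing-attributed adverse events.** NPWT groins: yes/no plus type (section 2.8.3). Standard-dressing groins: no item in section 2.7, 2.8.2, 2.8.3 or anywhere else in the article. The NPWT arm yields a proportion; the control arm has a denominator but no numerator.
2. **Unilateral cases** (about 95% of TEA and 90% of bypass, section 3.1). A risk difference needs a count from each arm. One is missing, so it cannot be formed.
3. **Bilateral cases** (about 5% of TEA and 10% of bypass). A paired comparison needs the yes/no result on both sides of the same patient. Only one side is recorded, so discordant pairs cannot be identified.
4. **Other harms in the same list.** Bleeding, lymphorrhea, sepsis, surgical revision, readmission at 30 days, reoperation at 30 days, 90 days and 1 year, and groin-related care contacts within 90 days are not tied to an arm. They can be compared.
5. **Whether those items stand in for dressing reactions.** Only in part. The ASEPSIS score includes erythema, a local skin sign, in both arms, but as a component of an infection and healing score that assigns no cause. A care contact for a groin problem misses reactions that led to no visit, and does not separate a reaction to the dressing from an infection.
6. **Endpoints.** SSI, seroma/lymphocele, hematoma and wound dehiscence do not draw on the dressing item, so their analysis is unchanged.

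What is missing is therefore one variable in one arm: reactions attributed to the standard dressing.

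**The case against.** The strongest reply is that this is a condensed variable list in a journal article. It names an item about the investigational device and does not say that control-dressing events go unrecorded; the full protocol and case report form are not shown and may hold a symmetric field. An NPWT-specific item also has a purpose of its own, since pump and suction exist in one arm only. And no objective or endpoint concerns dressing reactions.

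Much of this stands. It is why the point is minor, and why a device-specific item should be kept. It does not remove the point: the article is not silent on dressing adverse events, it words the variable for one dressing, and nothing in it suggests a counterpart. If the form is symmetric, only the text needs correcting.

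Three stronger readings are tempting, and the document supports none of them:

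- A reader might infer that the trial cannot compare safety between arms at all. It can, for the harms in step 4 of the check. Nor can these all be set aside as efficacy outcomes: bleeding, sepsis, readmission, reoperation and groin-related care contacts are not endpoints in section 2.2.
- A reader might suppose that the standard dressing is adhesive and occlusive and so known to harm skin. Section 2.7 says only that it is sterile, water-proof and padded. The point needs no more than that it is a dressing on the same kind of wound, whose background rate is unknown.
- A reader might try to express the loss as a confidence-interval width under assumed event rates. Such a width would describe the precision available after the fix, not the size of the defect.

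**Conclusion.** The point holds for reactions attributed to the dressing and no further. As worded, these cannot be compared between arms, nor between groins in bilateral patients. Other recorded harms remain comparable, and the primary and secondary results are untouched. Within that one variable the contrast is absent rather than imprecise; its importance in percentage points cannot be stated, because the article gives no reaction rate for either dressing.

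The conclusion assumes that data are collected as section 2.8.3 is worded and that the case report form holds no matching field for control groins. Severity is minor.

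**What to change.** - Reword the item to: 'Adverse events of the allocated wound dressing (yes/no) and type'.
- Collect it for every study groin in both arms, with the same form and the same time window counted from surgery, at the contacts that section 2.8 already provides (the one-month visit and the telephone interview after three months).
- Keep pump or suction events as a separate sub-item for NPWT only, outside the comparison. Because section 2.8.3 has the outpatient assessor unaware of the dressing, someone other than that assessor should fill in this sub-item.
- Report the risk difference between dressings with a 95% confidence interval that accounts for pairing in bilateral cases.

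The cost is one extra field in control groins and a question at contacts that already take place. For patients already past follow-up the control data may be incomplete; the report should say so and state from when the item was collected in both arms. If the form is already symmetric, correcting the sentence in section 2.8.3 is enough.
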